# Virtual Arm Boot Camp (V-ABC): study protocol for a mixed-methods study to increase upper limb recovery after stroke with an intensive program coupled with a grasp count device

**DOI:** 10.1186/s13063-022-06047-9

**Published:** 2022-02-08

**Keywords:** Stroke, Rehabilitation, Wearable sensor, Upper extremity, Arm use, Randomized controlled trial

## Abstract

**Background:**

Encouraging upper limb use and increasing intensity of practice in rehabilitation are two important goals for optimizing upper limb recovery post stroke. Feedback from novel wearable sensors may influence practice behaviour to promote achieving these goals. A wearable sensor can potentially be used in conjunction with a virtually monitored home program for greater patient convenience, or due to restrictions that preclude in-person visits, such as COVID-19. This trial aims to (1) determine the efficacy of a virtual behaviour change program that relies on feedback from a custom wearable sensor to increase use and function of the upper limb post stroke; and (2) explore the experiences and perceptions of using a program coupled with wearable sensors to increase arm use from the perspective of people with stroke.

**Methods:**

This mixed-methods study will utilize a prospective controlled trial with random allocation to immediate or 3-week delayed entry to determine the efficacy of a 3-week behaviour change program with a nested qualitative description study. The intervention, the Virtual Arm Boot Camp (V-ABC) features feedback from a wearable device, which is intended to increase upper limb use post stroke, as well as 6 virtual sessions with a therapist. Sixty-four adults within 1-year post stroke onset will be recruited from seven rehabilitation centres. All outcomes will be collected virtually. The primary outcome measure is upper limb use measured by grasp counts over 3 days from the wearable sensor (TENZR) after the 3-week intervention. Secondary outcomes include upper limb function (Arm Capacity and Movement Test) and self-reported function (Hand Function and Strength subscale from the Stroke Impact Scale). Outcome data will be collected at baseline, post-intervention and at 2 months retention. The qualitative component will explore the experiences and acceptability of using a home program with a wearable sensor for increasing arm use from the point of view of individuals with stroke. Semi-structured interviews will be conducted with participants after they have experienced the intervention. Qualitative data will be analysed using content analysis.

**Discussion:**

This study will provide novel information regarding the efficacy and acceptability of virtually delivered programs to improve upper extremity recovery, and the use of wearable sensors to assist with behaviour change.

**Trial registration:**

ClinicalTrials.govNCT04232163. January 18, 2020.

## Background

Stroke is a leading cause of adult disability, with 40–60% resulting in upper limb hemiparesis [1]. This hemiparesis is inversely related to upper limb function, ability to use the arm and hand, and performance of activities of daily living [2].

Thousands of repetitions of reaching to grasp may be necessary to bring about upper limb functional recovery following a stroke, as suggested from animal studies [3]. Current upper limb movement practice during rehabilitation typically involves a total dose that is far below that recommended based on animal studies [4, 5]. While intensive practice early in the recovery appears to lead to better outcomes [6], high levels of practice can also result in meaningful improvements in arm function even in chronic stroke [7, 8].

Encouraging daily upper limb use and increasing intensity of practice in rehabilitation are two important goals for optimizing upper limb recovery post stroke. However, motivating thousands of repetitions in scheduled practice, or over the day is challenging. Feedback from wearable sensors may be a novel way of achieving one or both of those goals. Feedback from accelerometers have been used to increase physical activity in older adults [9] but few studies have used accelerometers to increase upper limb use. One pilot RCT used a wrist-worn accelerometer that vibrated when arm activity levels were low and showed the protocol was feasible; however, statistical analysis was not performed on the small sample (*n* = 33) [10]. Wearable sensors can be used in the home and their data accessed by the therapist. Virtual online sessions are convenient for participants who do not need to travel to a rehab centre, thereby facilitating access to intervention for those living in remote and rural communities. Virtual sessions can avoid potential transmission of infectious diseases such as COVID-19.

This mixed-methods trial has objectives to (1) determine the efficacy of a clinician directed virtual behaviour change program using an RCT where the intervention incorporates feedback from a custom wearable sensor to help increase upper limb use post stroke; and (2) explore the experiences and perceptions of using wearable sensors with a virtual program to increase arm use from the perspective of patients with stroke. This RCT uses a delayed-entry control group since we are recruiting at a point where patients are no longer receiving any formal therapy, and hence would have minimal changes without any intervention. It is hypothesized that a clinician directed virtual behaviour change program that incorporates feedback from a wearable sensor to progress the intervention will result in greater increase in arm use compared to usual care.

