#### Participant population

Adults with stroke who have been discharged or about to be discharged from the stroke programs at each rehabilitation hospital will be screened for eligibility. Individuals will be included if they (1) are within 12 months of stroke onset (with confirmed ischaemic infarct or intracerebral haemorrhage); (2) have unilateral upper limb impairment; (3) live in the community; (4) have some ability to move their arm and hand (at least about 30° shoulder flexion or abduction and extend at least one finger and thumb from a flexed position); (5) are using their affected upper limb in a different way than prior to their stroke (Rating of Arm-use in the Community and Home (REACH) Scale < 5) (12); (6) completed formal physical and occupational therapy rehabilitation for the upper limb; (7) have access to a tablet, computer, laptop or phone with internet and email access; and (8) are willing and able to wear an activity monitor safely for their waking hours. If the participant has a caregiver, they will be invited to assist in this study; however, a caregiver is not required for participating in the study unless the participant requires assistance to utilize the internet or with other aspects of the protocol.

Individuals will be excluded from the study if they (1) have musculoskeletal/other neurological conditions that limit movement in their arm; (2) are unable to provide informed consent; (3) have another medical condition that would affect their ability to participate in the treatment protocol; (4) have persistent pain in their affected upper limb that affects their ability to use the limb; and (5) are unable to speak, understand, or read English. An exception for (5) will be made if the participant does not speak the English language but has another person (i.e. family member, caretaker or friend) who can be present and translate during evaluation/treatment sessions, and home activities related to the study.

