#### Secondary outcomes

##### Self-report affected arm use

The REACH Scale is a valid and reliable tool for capturing how people are using their affected arm and hand outside in the community setting [12].

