#### Sample size estimates

The sample size was calculated using G power. The study will require 32 patients per group to achieve 80% power at a level of significance of 0.05 to detect a large effect size (Cohen’s *f* = 0.4) using an ANCOVA model (controlling for baseline values) and a dropout rate of 20%.

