#### Data analyses

Descriptive statistics will be used to summarize data. Analysis of covariance will be used for the main analysis to estimate the differences comparing the 3-day hand counts at the post-treatment (immediately following the 3-week intervention) controlling for the baseline. Multiple imputation will account for missing data. The significance level will be set at 0.05, and all statistical tests will be two-tailed. Participant data will be analysed on an intention-to-treat basis. Confidence intervals (95% CIs) will be reported, where applicable. Secondary outcomes at post-treatment will follow the same analysis. In an additional analysis, we will use a mixed effects model to examine whether the intervention effects are retained at 2 months after the intervention ends.

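### Minimal untreated change is assumed for an open 0-to-12-month window after stroke, and the main ANCOVA omits time since stroke: a modest precision and interpretation point, not a bias

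*Protocol article*

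**What the plan says.** **Premise.** The Background section of the Protocol article explains the delayed-entry control by stating that "patients are no longer receiving any formal therapy, and hence would have minimal changes without any intervention".

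**Who can enter.** Under Participant population, criterion 1 is that participants "are within 12 months of stroke onset (with confirmed ischaemic infarct or intracerebral haemorrhage"). No minimum time is stated. Separate criteria require community residence and that arm rehabilitation has ended.

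**Randomisation.** Allocation is 1:1, stratified by site and by REACH score (below 3, or 3 and above). Time since stroke is not a stratifier.

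**Analysis.** Under Data analyses, the main ANCOVA estimates the difference by "comparing the 3-day hand counts at the post-treatment (immediately following the 3-week intervention) controlling for the baseline". Secondary outcomes at that time point follow the same analysis. The Sample size estimates section uses the same model, with baseline as the only covariate. Retention at 2 months is examined with a mixed effects model.

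**Follow-up.** Under Evaluations, the delayed arm is assessed 3 weeks after baseline, is then treated, and has its last assessment 2 months after its own treatment ends.

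**The concern.** The Background sentence draws two conclusions from one fact. That formal therapy has stopped is backed by an entry criterion. That little change will follow is backed by neither a time limit nor any data in the article. One participant may be weeks from stroke and another 11 months out, and both meet criterion 1.

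The baseline count records where a participant is, not how fast the arm is still recovering. If time since stroke predicts the 3-week count among people with equal baseline counts, a baseline-only ANCOVA leaves that variation in the residual. The interval for the treatment effect is then wider than it need be, and a chance difference between arms in time since stroke goes uncorrected.

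The premise carries more weight at 2 months. By then every participant has received the program, so no untreated comparison remains. A maintained or rising count could be a retained effect, continuing recovery or both.

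**Working it through.** **1. Inputs.** From the article: 32 per group (64 in total), Cohen's f = 0.4, 20% dropout, ANCOVA with baseline (Sample size estimates), with "80% power at a level of significance of 0.05 to detect a large effect size"; and "all statistical tests will be two-tailed" (Data analyses). Assumed: the partial R² between time since stroke and the follow-up count given baseline. The documents give no value, so 0 to 0.20 is used.

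**2. The plan's own figure.** For two equal groups d = 2f = 0.8. Power comes from the noncentral F with 1 and N − 3 degrees of freedom and noncentrality f²N.
- N = 52: noncentrality 0.16 × 52 = 8.32, power 0.807. This is the smallest N reaching 80%.
- Dropout: 52 / 0.8 = 65, against 64 stated. The plan's size reproduces to within rounding.
- Evaluable from 64: 64 × 0.8 = 51.2, taken as 51; power 0.799. There is no slack.

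**3. Adding time since stroke.** The residual SD shrinks by √(1 − R²), so f becomes 0.4/√(1 − R²), and one more degree of freedom is spent (N − 4).

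| Assumed partial R² | Fall in standard error | Power at 51 | Evaluable N for 80% |
|---|---|---|---|
| 0 | 0% | 0.799 | 52 |
| 0.05 | 2.5% | 0.819 | 49 |
| 0.10 | 5.1% | 0.839 | 47 |
| 0.20 | 10.6% | 0.879 | 42 |

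**4. Simulation (8,000 runs, 52 evaluable, covariates drawn at random).** The formula in step 3 takes the covariates as balanced between arms, so it is slightly generous.

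| Partial R² | Type I error without the covariate | Power without | Power with |
|---|---|---|---|
| 0 | 0.050 | 0.806 | 0.798 |
| 0.10 | 0.052 | 0.807 | 0.836 |
| 0.20 | 0.051 | 0.797 | 0.870 |

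Type I error stays at its nominal level without the covariate. A covariate with no prognostic value costs a little under one percentage point of power.

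**5. Chance imbalance.** With 26 and 25 analysed, the standard error of the between-arm difference in a baseline factor is √(1/26 + 1/25) = 0.280 SD. A difference above 0.3 SD is 0.3/0.280 = 1.07 standard errors, which has a two-sided probability of about 0.28. Its effect on the estimate is small: at R² = 0.10 it shifts the estimate by 0.3 × √0.10 = 0.09 residual SD. At 26 per arm the 95% range of such shifts, 1.96 × √(2/26) × √R², is ±0.12, ±0.17 and ±0.24 residual SD at R² = 0.05, 0.10 and 0.20, against a planned effect of 0.8. This restates the precision loss of step 3 and does not add to it.

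**6. Two-month analysis.** No arithmetic applies. The delayed arm is treated after its 3-week assessment, so at its 2-month visit it is no longer an untreated group. A covariate cannot replace the missing comparison.

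**The case against.** The strongest reply is that the primary comparison does not need the premise. It is randomised and concurrent, average recovery over 3 weeks occurs in both arms and cancels, and chance imbalance is already covered by the p-value and confidence interval. All of this stands. A reader might infer that the primary result is biased or its error rate inflated; the design and step 4 show otherwise.

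The gain is also assumed. Baseline counts and REACH stratification may already absorb part of the recovery signal, and 3 weeks is short. That stands, and is why the range starts at zero.

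Baseline-only ANCOVA is a standard, valid analysis, and an analysis plan that is not shown may add covariates. This stands in part: nothing in the article excludes another covariate. But the article does name its main model and sizes the trial on it, so a later addition should be prespecified.

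Two further readings are tempting and fail.
- The screening sentence, "Adults with stroke who have been discharged or about to be discharged from the stroke programs at each rehabilitation hospital will be screened for eligibility", might suggest that people still in a program are enrolled and that REACH, described as "capturing how people are using their affected arm and hand outside in the community setting", could not be rated in them. The sentence describes who is screened. The inclusion criteria still demand community residence and finished arm therapy, and nothing shows REACH or baseline wear being taken before discharge.
- The Background remark that "intensive practice early in the recovery appears to lead to better outcomes" might seem to contradict the premise. It concerns response to practice, not change without treatment, so there is no contradiction.

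**Conclusion.** The point holds as a modest matter of precision and interpretation. The inference from ended therapy to minimal change is unsupported for a window with no lower limit, and the stated main model does not use a baseline variable that could reduce residual variance. The 3-week comparison is valid as planned and no stated figure is wrong.

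The benefit of adjustment lies between nothing and about 8 percentage points of power at 51 evaluable by the formula, and somewhat less in simulation. It rests wholly on an assumed partial R² of 0 to 0.20, and on f = 0.4 being expressed in units of the baseline-adjusted residual SD.

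The 2-month analysis can describe whether gains persist. It cannot separate persistence from natural recovery.

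**What to change.** 1. **Data analyses:** prespecify time since stroke at randomisation, continuous (for example log days), as an additional covariate in the ANCOVA for the primary and secondary outcomes, and carry it in the multiple-imputation model.
2. **Background:** replace the claim of minimal change with a statement that some recovery is expected in part of the sample and is handled by the concurrent randomised control.
3. **Data analyses, 2-month model:** state that no untreated arm exists at that point and that maintained counts may include natural recovery.

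No change to eligibility or to the timing of baseline assessment is called for.

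**Cost.** One degree of freedom, a few sentences and no new data, because criterion 1 already requires time since onset to be ascertained. If the covariate is not prognostic given baseline, there is no gain and a loss of under one point of power. The change should be documented through the modification route described under Data monitoring. With about half the sample recruited (Trial status) and no interim analyses planned, it can still be fixed before outcomes are compared by arm.

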## Methods

This nested mixed-methods study will be comprised of a multi-centre, site-stratified, assessor blinded, parallel group, randomized controlled superiority trial with a 1:1 allocation ratio with an embedded qualitative study [11]. The control group is a wait-list group who receive the intervention after the active treatment group which facilitates recruitment and retention of participants. The design is open label with only outcome assessors being blinded so unblinding of participants will not occur. Figure 1 shows a flow diagram of the study procedures. The methods for the quantitative and qualitative components are described here separately. The intervention and evaluations will be virtual which will enable recruitment from a wider catchment, and the eventual application in local, as well as remote and rural communities.

**Fig. 1 Fig1:**
[figure not shown]
Flow diagram of mixed-methods study

### Quantitative component: randomized, controlled trial (RCT)

#### Setting

The RCT will recruit from 7 rehabilitation hospitals in Canada to maximize participant recruitment: GF Strong Rehabilitation Centre (Vancouver), Parkwood Institute (London), Foothills Hospital (Calgary), Riverview Health Centre (Winnipeg), Sunnybrook Health Centre (Toronto), Toronto Rehab Institute (Toronto) and Nova Scotia Rehabilitation and Arthritis Centre (Halifax). These sites are part of the Heart and Stroke Foundation Canadian Partnership for Stroke Recovery CanStroke Recovery Clinical Trials Platform. The coordinating centre will be the GF Strong Rehabilitation Centre led by Principal Investigator ([name]) and a central research team which will oversee the preparation of protocol and revisions, preparation of study documents (brochures, site training protocols, informed consent and data collection forms), publication of study reports, organization of steering committee meetings, data entry and analysis. The coordinating centre team will have access to the final data set. Individual sites will retain access to site-specific data as per contractual agreement between sites, and may request access to the final data set. The steering committee (authors of this paper) will provide agreement of the final protocol; oversee recruitment of participants at each site and liaise with study coordinator/principal investigator; review progress of study and agreeing (if necessary) on changes to the protocol to facilitate the progression and completion of study. The study team (site leads, investigators, staff coordinators) will meet at least every other week to provide trial oversight and review trial conduct, including recruitment efforts, protocol adherence and any adverse events.

#### Participant population

Adults with stroke who have been discharged or about to be discharged from the stroke programs at each rehabilitation hospital will be screened for eligibility. Individuals will be included if they (1) are within 12 months of stroke onset (with confirmed ischaemic infarct or intracerebral haemorrhage); (2) have unilateral upper limb impairment; (3) live in the community; (4) have some ability to move their arm and hand (at least about 30° shoulder flexion or abduction and extend at least one finger and thumb from a flexed position); (5) are using their affected upper limb in a different way than prior to their stroke (Rating of Arm-use in the Community and Home (REACH) Scale < 5) (12); (6) completed formal physical and occupational therapy rehabilitation for the upper limb; (7) have access to a tablet, computer, laptop or phone with internet and email access; and (8) are willing and able to wear an activity monitor safely for their waking hours. If the participant has a caregiver, they will be invited to assist in this study; however, a caregiver is not required for participating in the study unless the participant requires assistance to utilize the internet or with other aspects of the protocol.

Individuals will be excluded from the study if they (1) have musculoskeletal/other neurological conditions that limit movement in their arm; (2) are unable to provide informed consent; (3) have another medical condition that would affect their ability to participate in the treatment protocol; (4) have persistent pain in their affected upper limb that affects their ability to use the limb; and (5) are unable to speak, understand, or read English. An exception for (5) will be made if the participant does not speak the English language but has another person (i.e. family member, caretaker or friend) who can be present and translate during evaluation/treatment sessions, and home activities related to the study.

Consent will be attained by a site coordinator from each of the 7 sites. All data will be de-identified with a code prior to being transferred to the central site (University of British Columbia) where the final dataset will be stored. Initial screening will be checked from self-report over the phone. Following the screening, participants will complete an electronic consent form, facilitated by a site coordinator from each respective centre who will describe the study and answer questions about the study. Following consent, a second screening will take place with an online session to confirm the physical criteria and ensure that the videoconference software is working and the environment is appropriate for the assessment and treatment. There are no plans for collection of lab or biological specimens for genetic or molecular analysis in the current trial.

#### Randomization

Participants will be randomized after their baseline assessment at a one-to-one ratio to either the Immediate Virtual Arm Boot Camp (V-ABC) group or Delayed V-ABC group using an online, third-party, randomization service (www.randomize.net). Randomization will be in variable block sizes (to ensure allocation concealment) and stratified by site (to control for regional differences). Participants will also be stratified by the REACH score (< 3 and ≥ 3) [12]. A score of 3 separates those with mild versus moderately affected upper limbs.

#### Intervention

The intervention will be delivered by physical or occupational therapists who will be provided training over a 4-h online session. V-ABC is an intense program aimed at increasing affected upper limb movement practice delivered virtually. We define movement practice as a combination of traditional upper limb exercises (i.e. strengthening, fine motor and task-based practice) and incorporation of the affected upper limb into daily activities. The program consists of three major components: (1) Home version of the Graded Repetitive Arm Supplementary Program (H-GRASP) to increase functional capacity of the affected arm (13); (2) feedback from a wrist-worn sensor (called TENZR by Biointeractive Technologies); (3) initial treatment and follow-up treatment sessions (total 6 virtual sessions over a 3-week intervention with the first session 1.5 h, and then 1 h). The Home GRASP protocol is a self-administered exercise program that consists of range of motion, strengthening and fine motor activities [13].

